### 5.1.2 Placebo

The placebo is formulated as a dry powder that has excipient and calorie content similar to AXA1125 (see Table 2). Excipient content that is dissimilar to AXA1125 is as follows: soybean lecithin has been removed because it is not required to ensure sufficient wetting of the excipients in the placebo formulation, sodium citrate dihydrate has been added and the citric acid amount reduced in order to match the pH of AXA1125, and maltodextrin and sunflower oil powder have been added as fillers. Each placebo and AXA1125 sachet contain approximately 76 kcal and provide approximately 456 kcal/day to subjects regardless of the treatment arm.

The placebo will be supplied to closely match the aroma, appearance, color, and taste profile of AXA1125 as powder in sachets. The total number of sachets, packaging, constitution, and administration of placebo mirrors AXA1125 to maintain double blinding during the study.

Calories are primarily delivered by a combination of maltodextrin (~50.4 kcal per sachet, or up to 302 kcal per day based on 3.78 kcal/g) and sunflower oil powder (~21.5 kcal per sachet, or up to 129 kcal per day based on 7.38 kcal/g). In Study AXA1125-003, the additional calories delivered to the subjects receiving placebo with similar composition did not result in an increase in weight, HbA1c, fasting glucose, or the AUC of glucose in an oral glucose tolerance test from baseline to Week 16 (see the current version of the IB); assessments of weight and glucose homeostasis are included in this study.

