### 2.3.3 Safety and tolerability endpoints - Cohort A and B

The safety and tolerability endpoints are:

- AEs and serious adverse events (SAEs)
- Physical examination findings, including vital signs (siting systolic and diastolic blood pressure, heart rate, respiratory rate, body temperature, resting O_2_ saturation) and body weight
- Change in clinical laboratory assessments, including chemistry, hematology, and urinalysis

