## 6.6 Safety and Tolerability Assessments

The onset and increase of severity of AEs will be assessed on an ongoing basis. In addition, the safety and tolerability will be monitored by physical examination findings, including body weight; vital signs; and clinical laboratory assessments (chemistry, hematology, and urinalysis).

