**APPENDIX 1. SCHEDULE OF ASSESSMENTS - COHORT A**

|  | **Screenin**  **g** | **Treatment Period** | |  |  | **Follo w-up** |  |  |
| --- | --- | --- | --- | --- | --- | --- | --- | --- |
|  | **Visit 1** | **Visit 2 Baseline** | **Visit 3 (via Telephone)** | **Visit 4**  **EOT or ET** |  | **Visit 5**  **(via T elepho ne)** |  |  |
| **Day** | -28 to -1 | 1 | 14 | 28 | 35 | |  | For detail |
| **Week** | -4 to -1 | 0 | 2 | 4 | 5 | |  |  |
| **Window** |  |  | ±3 | ±3 | ±3 | |  |  |
| Informed consent | X |  |  |  |  | |  | 8.1.1 |
| Demographics | X |  |  |  |  | |  | 6.2 |
| Medical, surgical, and medication history | X |  |  |  |  | |  | 6.3 |
| Height, weight, and BMI | X |  |  |  |  | |  | 6.4 |
| Vital signs (BP, HR, RR, body temperature, and resting O_2_^a^) | X | X |  |  | X | |  | 6.6.2 |
| Echocardiogram^b^ | X |  |  |  |  | |  | 6.6.3 |
| Prior and/or concomitant medication | X | X | X |  | X | |  | 5.2 |
| Physical examination^c^ | X | X |  |  | X | |  | 6.6.1 |
| Magnetic resonance spectroscopy^d^ (^31^P-MRS and ^1^H-MRS) | X |  |  |  | X | |  | 6.8.1 |
| Blood and urine collection for local laboratory assessments^e^ | X | X |  |  | X | |  | 6.5;  APPENDIX 3 |
| Serum NT-pro BNP^f^ | X |  |  |  |  | |  | 6.10;  APPENDIX 3 |
| Alcohol breath test | X | X |  |  |  | |  | 6.6.4.3 |
| Blood/plasma collection for central laboratory assessments^g,h^ |  | X |  |  | X | |  | 6.5; 6.10;  APPENDIX 3 |
| Pregnancy testing (females with reproductive potential)^i^ | X | X |  |  | X | |  | 6.6.4.4 |
|  | **Screenin**  **g** | **Treatment Period** | | | **Follo w-up** | | |  |
|  | **Visit 1** | **Visit 2 Baseline** | **Visit 3 (via Telephone)** | **Visit 4**  **EOT or ET** | **Visit 5**  **(via T**  **elepho ne)** | | |  |
| **Day** | -28 to -1 | 1 | 14 | 28 | 35 | | |  |
| **Week** | -4 to -1 | 0 | 2 | 4 | 5 | | | For detail |
| **Window** |  |  | ±3 | ±3 | ±3 | | |  |
| 6-Minute Walk Test^j^ |  | X |  |  | X | | | 6.8.3,  SRM |
| Serum lactate^k^ |  | X |  |  | X | | | 6.8.4 |
| CFQ-11 PRO for fatigue^l^ | X | X | X |  | X | | | 6.8.2 |
| Treatment assignment |  | X |  |  |  | | | 5.1 |
| Study drug dispensing |  | X |  |  |  | | | 5.1.4 |
| Study drug self-administration^m^ |  | ← – – – – – – – – – – – – X – – – – – – – – – – – – _→_ | | |  | | | 5.1.3, 5.1.4 |
| Study drug compliance review |  |  | X n | X^n^ | X | | | 5.1.4 |
| AE assessment | X | X | X | X | X | | | 6.7 |

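### Body weight is a safety endpoint and section 5.1.2 says glucose homeostasis is assessed, but no post-baseline weight or quantitative glucose measure is scheduled

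*Protocol*

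**What the plan says.** Protocol section 5.1.2 describes the calorie content of the two products: "Each placebo and AXA1125 sachet contain approximately 76 kcal and provide approximately 456 kcal/day to subjects regardless of the treatment arm". It then cites a 16-week study of a placebo of similar composition, in which weight, HbA1c, fasting glucose and glucose AUC did not rise, and adds that "assessments of weight and glucose homeostasis are included in this study".

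The safety endpoints for both cohorts, in section 2.3.3 and in the synopsis, list physical examination findings with vital signs (the list ending "saturation) and body weight"). Section 6.6 repeats that "the safety and tolerability will be monitored by physical examination findings, including body weight".

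In both schedules, Appendix 1 for Cohort A and Appendix 2 for Cohort B, the row "Height, weight, and BMI" carries a single mark, at Screening. Section 6.4 says how weight is measured but names no further time point. Section 6.6.1 and the schedule footnotes make the examination after Screening a limited one that may take place if symptoms call for it, and they do not mention weight.

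Appendices 3 and 4 list HbA1c among the Screening laboratories only. Neither serum chemistry panel includes glucose or insulin. The only named glucose analyte is qualitative urine glucose. Section 6.5 presents these appendices as the full analyte list.

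**The concern.** The text promises information that the schedule does not collect. A site that follows the schedule will weigh each subject once, before treatment, and will never draw a blood glucose. The safety section of the report would then have a declared endpoint, body weight, with nothing after baseline to summarise. It would also have no quantitative glucose result to set beside the earlier study that section 5.1.2 cites.

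The gap has some practical weight. Both products add calories every day for four weeks, inclusion criterion 5 admits pre-diabetes with HbA1c up to 6.0%, and the exclusion criteria allow a BMI up to 35.

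**Working it through.** This is a check of text against schedule, so little arithmetic applies. The plan's own calorie figure is reproduced first.

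**Calorie figure.** Inputs from sections 5.1.2 and 5.1.4: about 76 kcal per sachet, 3 sachets per dose, 2 doses per day. 76 × 3 × 2 = 456 kcal/day, which agrees with the text. Over the 28 dosing days of section 3.1, 456 × 28 = 12,768 kcal. This is intake from the product in either arm, not net excess, because section 5.4 asks subjects to keep a diet stable in calories.

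**Scheduled measurements per subject**, read from Appendices 1 to 4:

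| Measure | Cohort A, up to Day 1 | Cohort A, on treatment | Cohort B, up to Day 1 | Cohort B, on treatment |
| --- | --- | --- | --- | --- |
| Body weight | Screening | none | Screening | none |
| HbA1c | Screening | none | Screening | none |
| Blood glucose | none | none | none | none |
| Urine glucose, qualitative | Screening, Day 1 | Visit 4 | Screening | Visit 4 |

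**What follows.** A change from baseline needs one value before treatment and one after. Weight and HbA1c have the first but not the second. Blood glucose has neither. For urine glucose, a shift between negative and positive can be tabulated, but no quantity.

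**Is the weight row an artefact of a damaged table?** In the text of Appendix 1 the Visit 4 marks have slipped one column to the right. They are still present in the rows for vital signs, spectroscopy and the walk test, whereas the weight row has no second mark anywhere. The Cohort B weight row is intact and shows the same single mark.

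**Does the repeated local draw contain glucose under another name?** The schedule footnotes describe that draw as blood count, chemistry and urinalysis, and the chemistry lists contain no glucose. The central laboratory and biomarker lists for Cohort A do not name it either. Metabolomics is planned in Cohort A as exploratory work, with no glucose analyte specified.

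**The case against.** The best counter-argument is that sections 2.3.3 and 6.6 place body weight within the physical examination findings, and both schedules mark an examination at Visits 2 and 4. On that reading the separate height and weight row serves only the BMI limit for entry, and weights could still be taken later. This has some force: it would be too strong to say that no post-baseline weight will exist. It does not remove the problem, because the later examinations are optional, depend on symptoms and do not mention weight, while weight has a schedule row of its own. Section 2.3.3 also attaches the word change only to the laboratory assessments, so the text does not explicitly promise a weight change. An on-study weight is still what an endpoint and a monitoring item imply.

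A reader might go further in two directions that the documents do not support.

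- One is that changes in weight and glucose cannot be evaluated at all. Qualitative urine glucose is repeated at Visit 4 in both cohorts, so a crude glycosuria shift can be seen.
- The other is that the protocol justifies its calorie-containing placebo by this monitoring, so that a safeguard has been withdrawn. Section 5.1.2 rests mainly on the earlier 16-week study. The clause on assessments follows as an addition and is not called a safeguard. Calories are matched between arms, exposure is 4 weeks, and HbA1c above 6.0% is excluded, so the calorie total measures neither bias nor risk.

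Both readings go too far, but the mismatch between text and schedule remains.

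**Conclusion.** The protocol contradicts itself. It names body weight as a safety endpoint and says that weight and glucose homeostasis are assessed, yet it schedules no post-baseline weight, no post-baseline HbA1c and no blood glucose at any visit. This applies to both arms of both cohorts, about 40 + 10 = 50 subjects.

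The conclusion assumes that the rows of Appendix 2 not legible here do not contain a second weight entry, and that the appendices are the full analyte list, as section 6.5 says.

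The consequence is limited to descriptive safety reporting. The primary endpoint, its analysis and the sample size are untouched. The point should be corrected, because a declared endpoint and a written statement are otherwise unsupported.

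**What to change.** Either of two routes removes the contradiction.

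**Measure what is promised.**
- Add weight at Visit 4 (EOT/ET) to Appendices 1 and 2. The Screening weight qualifies as baseline under section 7.4.5, which takes the last value before randomization. A weighing at Visit 2 is optional.
- Add serum glucose to the local chemistry panels in Appendices 3 and 4.
- In Cohort A, compare Visit 2 with Visit 4, drawn before the in-clinic dose so that the fast in section 5.5 covers both.
- In Cohort B, the chemistry panel runs at Screening and Visit 4, so compare those. Section 5.5 sets no fast for the Screening draw. It also ties the Visit 4 fast to biomarker sampling, which section 6.5 limits to Cohort A. Either state a fasting requirement for both Cohort B draws or record fasting status at each.
- Report that Cohort A subjects who finished before the change have no post-baseline values. Version 4.0 already cites Week 4 data from an interim look at Cohort A, so there are some. The number is not given, but it would be at least 10 if that look was the one planned in section 7.4.8.

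**Or claim less.** Delete body weight from the synopsis, section 2.3.3 and section 6.6, and the clause from section 5.1.2, so that no change in weight or glucose is claimed. Leaving the synopsis unchanged would create a new inconsistency.

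The first route costs an amendment, one weighing at a visit where vital signs are already taken, one analyte on an existing draw, and a fasting instruction or one extra data field in Cohort B. The second costs only the text change.

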###### Table 2 Excipient Function Within Placebo

| **Ingredient** | **Ingredient Function** |
| --- | --- |
| Maltodextrin, NF | Filler |
| Sunflower oil powder | Filler |
| Citric acid, anhydrous | pH adjuster |
| Sodium citrate, dihydrate,^1^ NF | Buffer, pH adjuster |
| Xanthan gum 180 | Thickening agent |
| Sucralose, powder | Sweetener |
| Orange flavor, natural and WONF | Flavor |
| Custard flavor, natural and artificial | Flavor |
| FD&C yellow no. 6 | Color |
| Low-substituted hydroxypropyl cellulose NBD-022 | Disintegrant |
| Colloidal silicon dioxide | Disintegrant |
| Magnesium stearate | Lubricant |

FD&C = food, drug, and cosmetic; NBD = New Binder Disintegrant; NF = National Formulary; WONF = with other natural flavors.

^1^ The total citric acid amount is distributed between citric acid and sodium citrate to ensure target pH. Total daily amount of citric acid matches the total daily amount in AXA1125.

Detailed information regarding the placebo formulation, constitution instructions, appearance, and storage requirements are described in the Pharmacy Manual.

### 5.1.3 Study drug storage

Study drug should be stored at a controlled room temperature, preferably between 15°C to 25°C (59°F to 77°F) at the study site. Subjects will be instructed to maintain the study drug in its cartons and/or kits at ambient temperature in a cool and dry environment until consumption.

### 5.1.4 Dosage, dose titration, and administration

At each dose, the 3 sachets will be constituted in ~6 fluid oz (~180 mL) of potable water to form a uniformly dispersed suspension. The suspension is to be self-administered orally as an orange-colored, orange-flavored drink, with or without food. Administration around mealtimes is recommended to promote compliance with the BID regimen and should occur at least 4 hours apart. The full dose needs to be taken within 30 minutes from the constitution of the study drug.

Constitution instructions are provided in the Pharmacy Manual.

### 5.1.5 Missed doses

If a subject misses a dose, then dosing should resume as soon as practical, so that the 2 doses are taken at least 4 hours apart. Study drug can be administered with or without food. Administration around mealtimes is recommended to promote compliance with the BID regimen.

### 5.1.6 Blinding

The subject, investigators, study site personnel involved in direct care of the subject will remain blinded. Personnel involved in the laboratory and image analysis will also remain blinded to the treatment assignment.

The Sponsor study team members will remain blinded to the treatment assignments during the study. A Sponsor biostatistician will be unblinded to perform the interim analysis and data monitoring.

AXA1125 and placebo will be identical in terms of the physical primary and secondary packaging. The primary and secondary packaging labeling will also be coded to prevent unblinding. The container closure system for the placebo will be the same heat-sealed foil sachet used for AXA1125. Additionally, the study drug will be packaged with blinded identifiers and secondary packaging (cartons) will be weight distributed to maintain the study blind.

The total number of sachets (3 sachets per dose) will be matched across all arms. The placebo closely matches the aroma, appearance, color, and taste of AXA1125 and will be constituted in the same ~6 fluid oz (~180 mL) volume of potable water.

Further details are provided in the Pharmacy Manual.

### 5.1.7 Accountability

The PI, pharmacist, and/or designee must maintain records of the study drug’s delivery to the study site, the inventory at the study site, the use by each subject, and the return to the Sponsor, clinical research organization (CRO), warehouse/drug distribution center, or alternative disposal of unused study drug. Subjects will be instructed to return all unused study drug to the study site or central location for study drug accountability reviews at the visits specified in the SOA (APPENDIX 1; APPENDIX 2). As applicable, the Sponsor, CRO, or warehouse/drug distribution center will maintain records of study drug disposal.

The records will include dates, quantities, batch/serial numbers, expiry (‘use-by’) dates, and unique code numbers assigned to the study drug and subjects. The PI, pharmacist, and/or designee will maintain records that adequately document that the subjects were provided the doses specified by the protocol and reconcile all study drug received from the Sponsor or delegate. At the time of return to the Sponsor/CRO, the PI, pharmacist, and/or designee must verify via documentation that unused or partially used study drug supplies have been returned by the subject and that no remaining study drug is in the study site’s possession.

Further details are provided in the Pharmacy Manual.

## 5.2 Medications, Supplements, Treatments, and Procedures

### 5.2.1 Concomitant medications and/or supplements

All concomitant medications and/or supplements taken within 4 weeks of Screening will be recorded on the eCRF. Medications and supplements to be reported in the eCRF include all prescription medications, over-the-counter medications, and other nonprescription medications or supplements taken by a subject. For this study, a prescription medication is defined as a medication that can be prescribed only by a properly authorized/licensed clinician.

Other than medications or supplements related to the subject’s standard of care therapy, there are no study-specific concomitant medications or supplements required by this study.

A stable regimen for lifestyle modifications and medication use is allowed as described in Section 5.2.2.

Any medication or vaccine (including over-the-counter or prescription medicines, vitamins, and/or herbal supplements) that the subject received within 4 weeks of Screening or receives during the study must be recorded along with the following:

- Reason for use;
- Dates of administration, including start and end dates; and • Dosage information, including dose, route, and frequency.

If clinically significant changes in any concomitant medications occur or if prohibited medication usage is required during the study, the PI should discuss with the Medical Monitor and Sponsor whether the subjects should continue in the study or be withdrawn.

### 5.2.2 Allowed medications, treatments, and/or procedures

Receipt of the following medications, treatment, and/or procedures are allowed during a subject’s participation in the study:

• A stable regimen (lifestyle modifications and/or medications) per the PI’s judgement, for at least 3 months prior to and during Screening, is allowed for the treatment of conditions that are well controlled, including mild hypertension, dyslipidemia, asthma (mild or not requiring chronic daily treatment), and/or hypothyroidism.

Note: Doses of certain medications (eg, statins, antihypertensives) used to treat stable chronic conditions may be modified during the study for safety or tolerability issues, if needed at the discretion of the PI.

### 5.2.3 Prohibited medications, treatments, and/or procedures

In addition to the medications, supplements and/or activities that are listed in the exclusion criteria (Section 4.2), the following are prohibited while a subject is participating in this study:

- Any new medications, doses, or regimens for the treatment of uncontrolled conditions, including mild hypertension, dyslipidemia, and/or asthma (mild or not requiring chronic daily treatment);

Note: Doses of certain medications (eg, statins, antihypertensives) used to treat stable chronic conditions may be modified during the study for safety or tolerability issues, if needed, at the discretion of the PI.

- Drugs that are known to cause myopathy, as in Exclusion Criterion 6;
- AA or protein supplements, carnitine, creatine, or Nac;
- Use of an investigational drug, product, or device, or enrollment in another study of an investigational drug, product, or device;
- Surgical procedure which may interfere with absorption of the study drug, including but not limited to resection of any part of the gastrointestinal tract, gastric or intestinal bypass, any bariatric surgery, or inflammatory bowel disease; or
- Organ transplant.

If there are questions regarding concomitant medications, the Medical Monitor should be consulted.

Should circumstances require the use of prohibited medication(s), medical treatment(s), or procedure(s) during the study, the PI should discuss with the Medical Monitor and Sponsor and assess whether to discontinue the subject from study drug or from the study in order for the subject to receive any necessary and appropriate medical care.

Subjects who have medical treatment(s) or procedure(s), which would otherwise prohibit entry into the study planned during the duration of the study will be deemed ineligible at the Screening Visit.

## 5.3 Prevention of Pregnancy

Subjects who are FCBP or males with a partner who is a FCBP must use a highly effective form of birth control from the day of the first dose of study drug, throughout the study, and for 30 days (females) or 90 days (males) after the last dose of study drug.

Definition of Female of Childbearing Potential and of Fertile Men

A female is considered of childbearing potential (ie, fertile) following menarche and until becoming post-menopausal unless permanently sterile. Permanent sterilization methods include hysterectomy, bilateral salpingectomy, and bilateral oophorectomy.

A postmenopausal state is defined as no menses for 12 months without an alternative medical cause. A high FSH level in the postmenopausal range may be used to confirm a postmenopausal state in women not using hormonal contraception or hormonal replacement therapy. However, in the absence of 12 months of amenorrhea, a single FSH measurement is insufficient.

A man is considered fertile after puberty unless permanently sterile by bilateral orchidectomy Birth Control Methods Which May be Considered as Highly Effective

A highly effective method is one that can achieve a failure rate of <1% per year when used consistently and correctly. The acceptable birth control methods for female subjects are:

- Combined (estrogen and progesterone- [progestogen-] containing) hormonal contraception associated with inhibition of ovulation, administered by oral, intravaginal, or transdermal routes;
- Progesterone- (progestogen-) only hormonal contraception associated with inhibition of ovulation, administered by oral, injectable, or implantable routes;
- Intrauterine device;
- Intrauterine hormone-releasing system;
- Bilateral tube occlusion;
- Vasectomized partner (provided the partner is the sole sexual partner of the FCBP subject and that the vasectomized partner has received medical assessment of the surgical success); or
- Complete sexual abstinence (ie, refraining from heterosexual intercourse; the reliability of sexual abstinence should be evaluated in relation to the duration of this study and the preferred and usual lifestyle of the subject).
- Note: True abstinence, when in line with the preferred and usual lifestyle of the patient, is considered a highly effective method only if defined as refraining from heterosexual intercourse during the entire period of risk associated with the study drug treatment. Periodic abstinence (eg, calendar, ovulation, symptothermal, or post-ovulation methods) and withdrawal are not acceptable methods of contraception.

The acceptable birth control methods for male subjects are:

- Barrier contraception (eg, latex condom with spermicide, diaphragm with intravaginal spermicide, or cervical cap with spermicide);

Note: Female partner use of a highly effective form of birth control (failure rate <1% per year) is acceptable for male subjects participating in the study.

- Vasectomy with documented azoospermia; or
- Complete sexual abstinence (ie, refraining from heterosexual intercourse; the reliability of sexual abstinence should be evaluated in relation to the duration of this study and the preferred and usual lifestyle of the subject).

Note: True abstinence, when in line with the preferred and usual lifestyle of the patient, is considered a highly effective method only if defined as refraining from heterosexual intercourse during the entire period of risk associated with the study drug treatment. Periodic abstinence (eg, calendar, ovulation, symptothermal, or post-ovulation methods) and withdrawal are not acceptable methods of contraception.

In addition to using a highly effective form of birth control, males will not donate sperm from the day of the first dose of study drug to 90 days after the last dose of study drug.

